### Monitoring

During the trial, some participants may be excluded from the study due to reasons such as abortion or IUFD below 20 wk of gestation or major fetal abnormalities or side effects of aspirin. In case of severe side effects and the need to discontinue the drug, the data will be placed in the data proportion of the discontinuation and will be removed from the final analysis. Since the trial is not blind for the researchers, they can access the results at any stage, due to the nature of the intervention.

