During the trial, some participants may be excluded from the study due to reasons such as abortion or IUFD below 20 wk of gestation or major fetal abnormalities or side effects of aspirin or discontinue the intervention. We will use the CONSORT checklist when writing our report.

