2. SGA (
<
 5
${\;}^{\text{th}}$
 centile) requiring delivery at 
<
 34 wk and 
<
 37 wk, which is measured by ultrasound.

3. Stillbirth or IUFD at 
≥
 20 wk, which is determined by ultrasound.

4. Spontaneous preterm delivery at 
<
 34 wk and 
<
 37 wk, which is determined by clinical examination and ultrasound.

5. Respiratory distress syndrome, described as the requirement for surfactant and ventilation due to prematurity, which is diagnosed by examination at the time of birth.

6. Ventilation requirement is defined as the need for positive pressure.

7. Neonatal intensive care unit admission, which is diagnosed by examination at the time of birth.

8. Neonatal anomaly, especially gastroschisis.

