#### Gathering of side effects and adverse incidents

Side effects are defined as any unwanted drug complications including hypersensitivity reactions, bleeding complications, headache, dizziness, nausea, vomiting, etc. Adverse events are defined as hospitalization for maternal and fetal observation, including bleeding course, spontaneous PTL, premature rupture of membranes, abortion, stillbirth, and the termination of pregnancy for fetal or maternal indications. Thirty days after the start of aspirin administration, a follow-up telephone interview was conducted with the participants to assess side effects and adverse events. If these events are considered a part of the normal development of the corresponding pregnancy, they will not be included in the category of drug-related complications but will be recorded in the clinical electronic records of the participants. If it is necessary to stop the drug permanently, the data will be placed in the data proportion of the discontinuation and will be removed from the final analysis.

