### Safety considerations

A physician assesses the possible role of the LDA if there are any significant adverse effects within therapy. If it is approved, the patient will be omitted from the study. Despite recording all the lost data about outcomes and follow-ups, it will not be included in the analysis. The discontinuation of treatment for pregnancies will be expressed by reason and study group.

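### Randomised women may be excluded for loss before 20 weeks or major fetal abnormality, although these are stated trial events, so neither is validly compared between arms as written

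*Protocol article*

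**What the plan says.** All references are to the protocol article.

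- **Exclusion, Monitoring section:** "some participants may be excluded from the study due to reasons such as abortion or IUFD below 20 wk of gestation or major fetal abnormalities". Side effects of aspirin are a further reason.
- **Exclusion, end of the Intervention section:** the same list in longer form, "abortion or IUFD below 20 wk of gestation or major fetal abnormalities or side effects of aspirin or discontinue the intervention".
- **Outcome, Secondary outcomes, item 8:** "Neonatal anomaly, especially gastroschisis".
- **Adverse events, Gathering of side effects and adverse incidents:** the definition includes "abortion, stillbirth, and the termination of pregnancy for fetal or maternal indications".
- **Omitted patients, Safety considerations:** after describing women taken out because a physician attributes an adverse effect to aspirin, the text adds "Despite recording all the lost data about outcomes and follow-ups, it will not be included in the analysis". It then promises a tabulation of treatment discontinuations by reason and arm.
- **Design:** the intervention arm starts aspirin before 11 weeks and the control arm after 11 weeks (Intervention). Participants and researchers are unblinded (Blinding), allocation is not concealed (Allocation mechanism), and researchers can see results at any stage (Monitoring).
- **Data form (Table II):** fetal death has an item only for losses after 20 weeks, and anomaly has none. The general item on side effects and adverse events is the only place on the form for either.

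**The concern.** The same events are both something to count and a reason to leave the study. Scans are planned at 11 to 13 6/7 weeks and at 18 to 22 weeks. A major abnormality found at either could take a woman out before outcome 8 is assessed at birth.

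The exclusions come after randomisation. The arms differ in aspirin exposure before 11 weeks, so early loss and malformation are events that the tested exposure could in principle affect. Dropping women for them conditions the comparison on something that may be a consequence of treatment. The choice is also discretionary, and it is made by staff who know the allocation.

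Two results are at stake. One is the comparison of early loss and anomaly between arms. The other is the pre-eclampsia comparison, which would be made in women selected after treatment began.

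**Working it through.** **1. The sections side by side**

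| Event | Counted as | Also a reason for exclusion |
|---|---|---|
| Anomaly | Secondary outcome 8 | Yes, if a major fetal abnormality (Intervention, Monitoring) |
| Abortion or fetal death below 20 weeks | Abortion is a defined adverse event | Yes (same sections) |
| Termination for fetal indication | Defined adverse event | Yes, where the indication is a major abnormality |

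No section sets an analysis of these events with all randomised women as denominator.

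**2. The plan's own sample size**

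Inputs from Sample size: 1.6% versus 4.3%, power 90%, alpha 5%, 1:1. Sidedness is not stated; two-sided is taken here. The difference is d = 0.027 and the mean proportion is 0.0295.

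- Uncorrected: n = [1.960·√(2·0.0295·0.9705) + 1.282·√(0.016·0.984 + 0.043·0.957)]² / 0.027² = about 823.2, rounded up to 824.
- With continuity correction: n = (823.2/4)·[1 + √(1 + 4/(823.2·0.027))]² = about 895.8, so **896**, as stated.
- With the 10% allowance: 896 × 1.10 = 985.6, so **986**, as stated.

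**3. How many women are open to exclusion**

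The documents give no rate of loss before 20 weeks or of major anomaly. The rates below are assumptions for illustration.

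- Loss of 5 to 15%: 0.05 × 986 = 49 and 0.15 × 986 = 148 per arm.
- Major anomaly of 2 to 3%: 0.02 × 986 = 20 and 0.03 × 986 = 30 per arm.

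**4. What keeping everyone would give**

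With equal rates p in both arms, the 95% half-width for the risk difference is 1.96·√(2p(1−p)/986).

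- Loss: 1.92 percentage points at p = 0.05 and 3.15 at p = 0.15.
- Anomaly: 1.24 points at p = 0.02 and 1.51 at p = 0.03.

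If every such pregnancy were excluded, the analysed count of these events would be near zero in both arms by construction.

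**5. Effect on power for pre-eclampsia**

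Power = Φ{[0.027·√n − 1.960·√(2·0.0295·0.9705)] / √(0.016·0.984 + 0.043·0.957)}, without continuity correction.

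- 10% loss to follow-up, then 5% excluded: n = 986 × 0.90 × 0.95 = 843, power 90.7%.
- 10% loss to follow-up, then 15% excluded: n = 986 × 0.90 × 0.85 = 754, power 87.3%.

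Power is therefore not the main problem.

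**6. Why one denominator is not enough for pre-eclampsia**

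Pre-eclampsia is defined only after 20 weeks, so a pregnancy lost earlier cannot have it. Suppose the rate among pregnancies reaching 20 weeks were 4.3% in both arms, with early loss of 10% in one arm and 15% in the other (illustrative values within the range above). Over all randomised, the rates would be 0.90 × 4.3% = 3.87% and 0.85 × 4.3% = 3.66%. The arm with more losses looks better by 0.2 points with no effect on pre-eclampsia. Restricting to pregnancies that reach 20 weeks removes this artefact but gives up the randomised comparison. Both results are needed, with early loss beside them.

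**The case against.** The strongest reply is that little is actually lost.

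- The exclusion wording is permissive.
- The explicit removal from the final analysis is attached to stopping the drug, and the non-analysis sentence in Safety considerations follows women with adverse effects attributed to aspirin.
- Abortion and termination are recorded as adverse events, and unusual events, imaging and delivery data go into the electronic file. Descriptive statistics by arm and a CONSORT report are promised.
- Because pre-eclampsia is defined only after 20 weeks, an at-risk denominator is a recognised choice.

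Much of this stands, and it rules out three stronger readings that a reader might infer.

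- **That fetal safety cannot be estimated.** The events are recorded, so a crude count over all randomised could be recovered. What fails is the comparison as the text now sets it.
- **That the plan itself declares a malformation concern.** The Introduction mentions earlier observational signals, including gastroschisis, mainly to contrast them with trial and other large-study findings of no association overall.
- **That the telephone interview 30 days after aspirin start leaves the arms unequally observed.** This needs randomisation and start weeks that the documents do not give. Side effects are also asked about at each clinic visit, and both arms have the same scans.

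The reply does not remove the conflict itself. The exclusion is stated twice, it covers a listed outcome and listed adverse events, and discretion in an open-label trial adds to the risk of bias. Nor is it an effect of a condensed article: the Accessibility of data section describes the text as the complete protocol.

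**Conclusion.** The point holds as a contradiction with consequences for bias. The Intervention and Monitoring sections allow randomised women to be excluded for events that the outcome and adverse-event sections undertake to count. Since the arms differ in exposure before 11 weeks and those deciding know the allocation, the exclusions could depend on treatment. Early loss and anomaly are then not validly compared between arms as written.

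The size cannot be taken from the documents. At an assumed early loss of 5 to 15%, about 49 to 148 of 986 women per arm are open to exclusion, fewer if the discretion is used sparingly. The loss of power is small. The direction of any bias is unknown, because it depends on how losses and exclusions fall between arms.

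**What to change.** 1. Delete loss below 20 weeks and major fetal abnormality as reasons for exclusion from the study and the analysis. Reconcile the Intervention, Secondary outcomes, Gathering of side effects and adverse incidents, Monitoring and Safety considerations sections accordingly. This concerns data and analysis sets only, not clinical management.
2. Keep every randomised pregnancy in its allocated arm, and restore from the electronic file any woman already taken out for these reasons.
3. Report by arm, with all randomised as denominator, loss below 20 weeks and any anomaly detected before or at birth, including in terminated or lost pregnancies.
4. For pre-eclampsia, analyse all randomised women and also show the result among pregnancies reaching 20 weeks. Put early loss beside both, so that fewer cases caused by more losses are not read as benefit.
5. Add an anomaly item and a loss-below-20-weeks item to Table II.

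The cost is wording in five sections and two form items. Most of the data are already collected, and no change to sample size is needed for this point.

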### Safety considerations

A physician assesses the possible role of the LDA if there are any significant adverse effects within therapy. If it is approved, the patient will be omitted from the study. Despite recording all the lost data about outcomes and follow-ups, it will not be included in the analysis. The discontinuation of treatment for pregnancies will be expressed by reason and study group.

### Ethical considerations

The trial was verified by the ethics committee of the Tehran University of Medical Sciences, Tehran, Iran Institutional Review board (Code: IR.TUMS.IKHC.REC.1401.215) on October 18, 2022, and steered conforming to the Declaration of Helsinki and later reconsiderations.

Written informed consent was acquired from all participants by the interviewer who included perinatology fellowship or prenatal clinic treatment staff. Participants are informed that their participation is voluntary and they may withdraw from the trial at any time without negative consequences on their treatment. The trial was registered on January 7, 2023, at the Iranian Registry of Clinical Trial (http://www.irctir/; IRCT ID: IRCT20221126056611N1). The last registry update was confirmed on 2023–12-21.

### Trial status

Employment for the pilot study began in January 2023 and is expected to end by December 2023. Additionally, recruitment for the main RCT was started in October 2023.

### Statistical analysis

For all primary analyses, the intervention group will be compared to the control group. Statistical analyses will be performed using STATA statistical software version 17.0 (STATA Corp, Texas, USA) and SPSS version 25 (SPSS, Inc., Chicago, IL, USA). Descriptive data will be reported as the mean 
±
 SD, median (IQR), or count (percent) as appropriate. The Shapiro-Wilk normality test will be applied to test the normality of the quantitative data. Continuous data will be compared between 2 groups using an independent sample *t* test or Mann-Whitney U test, and categorical data will be compared using the Chi-square test. Finally, to find the independent effect of aspirin treatment in high-risk participants a multiple logistic regression test will be used, in which the effect of aspirin treatment will be adjusted for the background variables of the participants that will differ between the 2 groups. The level of significance was 
<
 0.05. A complete set of descriptive statistics will be produced for all variables overall and by the treatment group. Graphical displays will be produced as appropriate.

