### Sample size

The sample size estimation of the main RCT was based on data from the ASPRE trial (6). The results of this trial showed that preterm PE occurred in 1.6% of the intervention group as compared with 4.3% in the placebo group. We calculated that the enrollment of 1792 participants in a 1:1 ratio of distribution (896 participants in each group) would provide the trial with a power of 90% (alpha level of 5%). If we are allowed a 10% loss to follow-up, the sample size will reach 986 participants in each group. A total of 1972 eligible participants will be randomly selected to participate in the trial arms. Furthermore, we proposed a sample size of 200 high-risk pregnancies in the pilot study and quality control. By screening 1686 pregnant women who attended the Maternal-Fetal hospital Clinic, we achieved this sample size. From January 2023, after obtaining written conscious consent, the trial began with 100 participants in each group at a 1:1 ratio, randomly.

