**Patient information**	
**Maternal demographic characteristics**	
**1**	Record of hypertension in a prior pregnancy
**2**	Chronic hypertension
**3**	Autoimmune disease: APs, SLE
**4**	Renal disease
**5**	Type 1 or 2 diabetes mellitus
**6**	Multiple fetuses
**7**	Nulliparity
**8**	History of PE in the mother or sister
**9**	BMI ≥ 30
**10**	Age ≥ 35
**11**	Low level socioeconomic
**12**	IVF
**13**	Obstetrical risk factors included SGA, PTL

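### The logistic regression picks its covariates by observed baseline imbalance; a short list fixed in advance on prognostic grounds should replace that rule

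*Protocol article*

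**What the plan says.** The Statistical analysis section first plans simple group comparisons, in which "categorical data will be compared using the Chi-square test". It then says that "to find the independent effect of aspirin treatment in high-risk participants a multiple logistic regression test will be used", and that in this model "the effect of aspirin treatment will be adjusted for the background variables of the participants that will differ between the 2 groups". It names no covariate, gives no threshold for differing, and does not say whether the chi-square test or the regression decides.

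Other sections bear on this:

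- **Inclusion criteria** rank prior pre-eclampsia, chronic hypertension, diabetes, renal disease, autoimmune disease and multifetal gestation as major risk criteria.
- **Table 2 (Data collection form)** records 13 baseline risk items. They include chronic hypertension, multiple fetuses and, as item 1, "Record of hypertension in a prior pregnancy".
- **Sequence generation** describes block randomisation and mentions no stratification factor.
- **Allocation mechanism** states that there was no concealment.
- **Blinding** says that neither participants nor researchers are blinded, but that a blinded analyst makes the assessments. **Monitoring** adds that researchers can see results at any stage.

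**The concern.** A covariate helps in a randomised comparison because it predicts the outcome. Whether it happens to be unbalanced is a different property. Under proper randomisation an observed difference is a chance event and says nothing about prognosis. A rule based on imbalance therefore tends to omit strong predictors that are balanced and to admit weak ones that are not.

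Three things are at stake. First, the adjusted odds ratio is conditional on whichever covariates enter, so its meaning varies with the draw. Second, the power available from known predictors is mostly given up. Third, with no definition of *differ* or of the set of background variables, someone has to decide what goes in, and the people running the trial are unblinded and may see results.

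**Working it through.** **1. The plan's own figure.** Inputs from Sample size: "preterm PE occurred in 1.6% of the intervention group as compared with 4.3% in the placebo group", 90% power, 5% alpha, 1:1 allocation. Sidedness is not stated; two-sided is assumed. With pooled variance, p̄ = (0.043 + 0.016)/2 = 0.0295 and difference d = 0.027:

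- n = [1.960·√(2·0.0295·0.9705) + 1.2816·√(0.043·0.957 + 0.016·0.984)]² / 0.027² = (0.4690 + 0.3057)² / 0.000729 ≈ 823.2, so 824.
- Continuity correction: (n/4)·[1 + √(1 + 4/(n·d))]² = (823.2/4)·(2.0863)² ≈ 895.8, so 896.

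The stated 896 per arm is reproduced exactly. The calculation uses no covariates, so a prespecified list does not alter it.

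**2. How often covariates enter under the rule.** Assumptions: *differ* means p<0.05, randomisation is proper, and the 13 items in Table 2 are independent.

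- A given strong factor enters with probability 0.05 and is left out with probability 0.95.
- At least one of 13 enters: 1 − 0.95¹³ = 1 − 0.513 = 0.487.
- Expected number entering: 13 × 0.05 = 0.65.
- Distribution: none 51%; one 13·0.05·0.95¹² = 35%; two 78·0.05²·0.95¹¹ = 11%; three or more about 2.5%.

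**3. What the rule does to the test.** Illustrative simulation with 3,000 runs per scenario and 896 per arm. There are 13 independent binary factors. One is prognostic, with prevalence 30%; the other 12 are unrelated to outcome, with prevalence 20%. Event risk is 4% in control women without the prognostic factor. The treatment odds ratio (OR) is 1.0 for type I error and 0.6 for power. None of these settings except 896 and the count of 13 comes from the documents.

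| Prognostic OR | Quantity | Unadjusted | Chosen by imbalance | Prespecified factor |
|---|---|---|---|---|
| 4 | Type I error | 4.7% | 4.6% | 4.7% |
| 8 | Type I error | 5.3% | 5.1% | 5.0% |
| 4 | Power | 69.0% | 69.1% | 70.1% |
| 8 | Power | 77.8% | 77.9% | 81.4% |

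The prognostic factor was selected in 4.5% to 5.4% of runs, and at least one factor in 47% to 49%, which agrees with step 2. Prespecified adjustment gained 1.1 points (OR 4) and 3.6 points (OR 8). Selection by imbalance recovered about 0.1 point in each case. Simulation error on a single power of 69% is √(0.69·0.31/3000) ≈ 0.8 point. The methods were compared on the same simulated trials, but the 1.1-point gain should still be read as small and approximate.

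**The case against.** The strongest reply is that little harm is shown. The rule looks at baseline data and not at the outcome, an unadjusted comparison is also planned, and the power at issue is modest. That stands, and it limits the point. Several stronger readings are tempting and are not supported:

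- **That p-values and intervals from the chosen model are invalid.** Type I error was 4.6% to 5.3% for all three methods when the rule was applied mechanically. Interval coverage was not examined separately.
- **That the model will be unstable because events are few.** The sample-size rates give 896 × (0.043 + 0.016) ≈ 53 events, but these are preterm pre-eclampsia. The primary outcome covers early-onset and late-onset disease, so also term cases, and the documents give no rate for it here. The rule also admits only 0.65 covariates on average, fewer than a fixed list of three, so this argument would count against the fix.
- **That the result will be picked from two analyses.** The text puts the regression last and presents it as the independent effect, a blinded analyst is mentioned, and naming the primary test may be left to an analysis plan not shown. What remains is discretion: the criterion is undefined and researchers can see results.
- **That every imbalance would be chance.** Without concealment, and with women removed after randomisation, imbalances may be systematic, and adjusting for them then has some rationale. A significance screen can still miss a modest imbalance in a strong predictor, so this too favours a fixed list.

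The point cannot be deferred to an unseen analysis plan as a mere omission. The article states a selection rule, and a later plan would have to contradict it.

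**Conclusion.** The point holds as a poorly fixed rule that is almost free to improve, and not as a threat to the trial's validity. On the assumed p<0.05 threshold and proper randomisation, a given strong recorded predictor is left out about 95% of the time. With independent factors as well, at least one of the 13 enters by chance about 49% of the time. The cost is a data-dependent adjusted estimate and roughly 1 to 4 points of power forgone. The power figure rests on assumed prevalences, event risk and odds ratios, and would differ with other inputs. No inflation of type I error is shown; the remaining risk is the discretion left by an undefined criterion in an open-label trial.

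**What to change.** Replace the rule in Statistical analysis with a short, named covariate list chosen on prognostic grounds from items already on the data form: for example chronic hypertension, hypertension in a prior pregnancy, and multifetal gestation. Keep these in the model whatever the observed balance, and do not use baseline comparisons to build it. State that this prespecified adjusted model is the primary analysis and that the unadjusted chi-square test is supportive.

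Item 1 of the form records hypertension in a prior pregnancy, and prior pre-eclampsia has no separate item. The list should use the variable as collected, or the form would need an added item.

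Trial status says that main-trial recruitment started in October 2023, so the list should be dated and fixed before any comparison of outcomes by arm. The cost is one paragraph of wording, with no new data for the example list and no change to the 896 per arm.
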